# A phase 3 study of ravulizumab to protect patients with chronic kidney disease from cardiac surgery-associated acute kidney injury and major adverse kidney events (ARTEMIS)

**DOI:** 10.1186/s13063-025-08895-7

**Published:** 2025-05-30

**Keywords:** Cardiac surgery-associated acute kidney injury, Cardiopulmonary bypass, Chronic kidney disease, Complement activation, Interventional study, Ischemia–reperfusion injury, Ravulizumab

## Abstract

**Background:**

Cardiac procedures, particularly those requiring cardiopulmonary bypass (CPB), are associated with the development of cardiac surgery-associated acute kidney injury (CSA-AKI). Development of CSA-AKI occurs as a result of inflammation, uncontrolled complement activation, and kidney cell damage. In patients with preoperative renal impairment, such as those with chronic kidney disease (CKD), there is an increased risk of both CSA-AKI and poorer clinical outcomes. Currently, there are limited effective, targeted pharmacological interventions for the prevention or treatment of CSA-AKI, although emerging therapies are being investigated, particularly in patients with existing CKD. The ARTEMIS (R*A*vulizumab to P*R*otect Pa*T*ients with Chronic Kidney Dis*E*ase fro*M* CSA-AK*I* and *S*ubsequent Major Adverse Kidney Events) trial will assess the efficacy and safety of ravulizumab (a complement C5 inhibitor) in reducing the risk of major adverse kidney events (MAKE) in patients with preoperative CKD undergoing non-emergent cardiac surgery with CPB.

**Methods:**

This trial is currently recruiting patients with CKD who have planned cardiac surgery requiring CPB including coronary artery bypass grafting, valve replacement or repair, or combined procedures. This is a phase 3, randomized, double-blind, placebo-controlled, global study assessing the efficacy and safety of a single preoperative dose of ravulizumab. These outcomes will be assessed using the occurrence of MAKE and its components, as well as the occurrence and severity of CSA-AKI throughout the study period.

**Discussion:**

Complement activation is known to occur during and after cardiac procedures as a result of CPB and ischemia–reperfusion injury, leading to a cycle of cell damage and death. Therefore, it is hypothesized that preoperative administration of ravulizumab will provide immediate and complete complement inhibition, which will be sustained throughout the surgical period, preventing the uncontrolled complement activation associated with the development of CSA-AKI, thus minimizing poor outcomes for patients.

**Trial registration:**

ClinicalTrials.gov NCT05746559. Registered on February 27, 2023.

**Supplementary Information:**

The online version contains supplementary material available at 10.1186/s13063-025-08895-7.

## Background

Cardiac surgery-associated acute kidney injury (CSA-AKI) is a common postoperative complication, particularly following procedures conducted on cardiopulmonary bypass (CPB). Development of acute kidney injury (AKI) is associated with substantial morbidity—including increased infection risk, prolonged mechanical ventilation, development/progression of chronic kidney disease (CKD), need for kidney replacement therapy (KRT), and higher rates of hospital readmission—alongside increased mortality [1, 2]. The composite endpoint of major adverse kidney events (MAKE) is comprised of the following variables: mortality, requirement for KRT, and sustained kidney dysfunction (≥ 25% decline from baseline in estimated glomerular filtration rate (eGFR)). Clinical trials investigating AKI routinely include MAKE as a key efficacy outcome, as the components are easily quantifiable indicators of kidney function [3, 4]. Patients with CKD are at a substantially increased risk of developing CSA-AKI (> 50% vs ~ 25%) and MAKE, leading to higher rates of long-term mortality (1–5 years post-surgery) compared with patients without prior CKD [2, 5–7]. Currently, there are limited effective, targeted pharmacological interventions for the prevention or treatment of CSA-AKI, and several therapies have failed to demonstrate efficacy in clinical studies [2, 8–10]. A recently completed phase 3 trial of amino acid infusion prior to cardiac surgery demonstrated positive efficacy (particularly in patients with CKD); however, the effectiveness of this approach remains to be fully elucidated and validated in real-world clinical practice [11–14]. Further trials are planned for other therapeutic approaches [15, 16].

In addition to the general risks associated with surgery, kidney injury may occur due to inflammation and hypoperfusion triggered by CPB [17]. Kidney hypoxia can cause injury to and death of both tubular epithelial cells and kidney endothelial cells, while further injury may also occur upon reperfusion. This process, termed ischemia–reperfusion injury (IRI), is a key driver of CSA-AKI pathogenesis [17, 18]. Additionally, direct contact between the blood and CPB circuitry, alongside shear stress on red blood cells whilst on bypass, are both known to cause hemolysis [19, 20]. This results in the generation of free heme which induces oxidative stress and, in addition to subsequent damage to kidney cells, causes the release of proinflammatory mediators, damage-associated molecular patterns, and direct activation of the complement system [20–22]. Complement activation results in the formation of the proinflammatory anaphylatoxins C3a and C5a, and the cytolytic membrane attack complex (MAC, C5b-9) [23]. These components of the terminal complement cascade cause further damage to kidney cells, perpetuating and amplifying a cycle of inflammation and injury [24, 25].

Ravulizumab, a humanized monoclonal antibody, binds complement C5 and provides immediate, complete, and sustained inhibition of the terminal complement pathway [26, 27]. Ravulizumab has a well-established safety and tolerability profile and is already approved for use in several complement-mediated disorders [26, 28–30]. Preventing injury to the kidney by inhibiting terminal complement may result in a decrease in the incidence, severity, and duration of CSA-AKI and reduce consequent MAKE. Proof of concept for this efficacy effect is derived from published reports of the effectiveness of C5 inhibition in patients with aHUS undergoing kidney transplantation, patients undergoing coronary artery bypass grafting with CPB, and higher-risk cardiac surgery patients [31–34].

Here we describe the study design for ARTEMIS (R*A*vulizumab to P*R*otect Pa*T*ients with Chronic Kidney Dis*E*ase fro*M* CSA-AK*I* and *S*ubsequent Major Adverse Kidney Events) which will assess the efficacy and safety of ravulizumab in reducing the risk of MAKE in patients with preoperative CKD undergoing non-emergent cardiac surgery with CPB (NCT05746559).

## Methods

SPIRIT guidelines were followed in the reporting of this trial [35]. The completed SPIRIT checklist can be found in Additional File 1, and the SPIRIT Figure detailing the full study schedule is included as Fig. 1.

**Fig. 1 Fig1:**
[figure not shown]
SPIRIT Figure study period schedule

### Study design

ARTEMIS is a phase 3, randomized, double-blind, placebo-controlled, global study of ravulizumab in adult participants with CKD undergoing non-emergent cardiac surgery requiring CPB for coronary artery bypass graft (CABG), valve replacement or repair, or combined procedures. The primary objective of this study is to assess the efficacy of ravulizumab in reducing the risk of MAKE at 90 days following surgery with CPB (MAKE90).

Participants are included on the basis of having preoperative CKD and considered at risk for further kidney events after CPB due to preoperative eGFR values of ≥ 20 to < 60 mL/min/1.73 m^2^ and a minimum Society of Thoracic Surgeons (STS) Calculator Renal Failure Risk Score of ≥ 2.8%; the STS score will be calculated during the initial screening period. The STS Calculator is a model which utilizes patient characteristics and baseline clinical data to generate procedure-specific risk scores for patient outcomes [36, 37]. Participants are identified by qualified research staff via methods including review of medical records, external referrals, or use of databases. Recruitment strategies may include study posters, referral letters, recruitment brochures, advertisements, social media posts, and websites, where permitted by local regulations. All recruitment materials will be submitted to local institutional review boards/ethics committees for review and approval, as required, prior to use. This will be a global study conducted in at least 19 countries.

Following the initial 28-day screening period, randomization and dosing will occur within 7 days prior to surgery with CPB (Fig. 2). Participants will be assessed on Days 3, 7, 15, 30, 60, and 90 after surgery (primary evaluation period), with the primary endpoint analysis conducted at Day 90 post CPB (primary analysis). Serum creatinine (sCr) and serum cystatin C (sCysC) will be measured on the day of screening (baseline); day of dosing (day 1); day of surgery (prior to induction of anesthesia), daily from days 1 to 7; on days 15, 30, 60, and 90 post CPB; and at hospital discharge. Baseline eGFR is reported as the average eGFR calculated from the last assessment during the screening and day 1 visits, prior to study intervention administration. Participants will be contacted by telephone at one year post CPB to assess the requirement for KRT and survival (survival follow-up period). The total study duration is approximately 400 days. A participant will be considered to have completed the study once they have completed the primary evaluation period or withdrawn.

**Fig. 2 Fig2:**
[figure not shown]
ARTEMIS study design. *Weight-based dosing will ensure ravulizumab serum concentrations of ≥ 175 μg/mL and achieve complete terminal complement inhibition, while maintaining maximum ravulizumab serum concentrations below the highest observed value of 3000 μg/mL from all completed clinical studies, for ≥ 18 days in the target population

A global, multidisciplinary executive steering committee (ESC) of independent experts in the field was established in 2023. Since its inception, the ESC meets every 6 months, providing input into the ravulizumab CSA-AKI global clinical development program and acting in an advisory capacity to Alexion on the study. The study started in April 2023, and the current estimated completion date is February 2027.

### Study endpoints

The primary endpoint in this study is the occurrence of MAKE90, defined as meeting at least one of the following events post CPB: initiation of KRT or death from any cause through day 90, or a decrease from baseline eGFR of ≥ 25% at day 90 calculated using the CKD-EPI equation and sCysC. This endpoint was chosen following discussions with and recommendations from both the Food and Drug Administration (FDA) and European Medicines Agency (EMA). The primary estimand is the population-level treatment difference between the two treatment groups in the proportion of participants experiencing MAKE90. The primary analysis will be based on the intent-to-treat (ITT) analysis set, which consists of all participants randomized to study intervention, under the treatment policy strategy. In this strategy, the values of the outcome of interest are used regardless of the occurrence of any intercurrent events. The treatment difference will be estimated using the Cochran-Mantel Haenszel (CMH) method adjusting for the two stratification variables (surgery type and baseline CKD stage). For the primary endpoint, missing data for KRT initiation or death will be imputed as a non-event, and missing eGFR values will be handled by multiple imputation in two steps. First, data will be imputed using Markov chain Monte Carlo to create a monotonic missing data pattern; then the second step will use the regression method for monotone missing data to impute the remaining missing observations. Rubin’s rule will be used for combining results to yield multiple imputation point estimates and standard errors. To minimize the risk of missing data, Alexion have a variety of patient retention initiatives including, but not limited to: home health and telehealth options for patients located substantial distances from clinical centers; clear and frequent communications provided to sites on the importance of complete data collection; active engagement with sites where patients are lost to follow-up to improve retention; and active site monitoring throughout the study. This allows for any issues to be addressed as they arise and prevents the development of more substantial complications.

Analysis of key secondary endpoints will also be based on the ITT analysis set and will include the occurrence and severity of Kidney Disease: Improving Global Outcomes (KDIGO)-defined AKI; length of post-operative intensive care unit stays; occurrence of KRT or mortality; and all-cause mortality. The primary assessment of MAKE90 will be based on sCysC measurements, as it is known that skeletal muscle atrophy (a common complication of cardiac surgery) can decrease sCr levels, leading to overestimation of eGFR after cardiac surgery [38, 39]. The secondary endpoints measuring AKI occurrence will be based on the sCr measurement. Additional secondary endpoints include MAKE assessed at days 30 and 60 post CPB using eGFR calculated from sCr or sCysC, MAKE assessed at day 90 post CPB using eGFR calculated from sCr, and occurrence of STS renal failure as determined by the Risk, Injury, Failure, Loss of kidney function, and End-stage kidney disease (RIFLE) Failure criteria. The proportion of participants meeting each of the key secondary endpoints will be summarized by treatment group. The point estimates and associated 2-sided 95% confidence intervals of the treatment difference in proportions will be estimated using the CMH method. Healthcare resource utilization will be assessed by documenting and comparing the length of total index hospital stays, number of days on mechanical ventilation, hospital readmissions, and days on KRT between treatment groups. Safety, pharmacokinetics and pharmacodynamics, and patient-reported outcomes of health-related quality of life will also be assessed. Exploratory endpoints in this study include exploration of the efficacy of ravulizumab in reducing the risk of CSA-AKI within 7 days of CPB, measured via sCysC (highest AKI stage by KDIGO criteria and/or occurrence of severe AKI [KDIGO stage 2 or 3]), and the assessment of biomarkers at baseline and following treatment. Biomarkers include, but are not limited to: complement pathway activation (plasma and urine sC5b-9), renal injury (urine neutrophil gelatinase-associated lipocalin), and endothelial damage (plasma thrombomodulin).

A series of subgroup analyses of the primary endpoint and key secondary endpoints are planned, including in the following participants: different races; different sexes; different age groups (18–60, 61–75, > 75 years); different CKD stages at baseline; and different surgical types during CPB.

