### Study assessments and procedures

Study inclusion and exclusion criteria are listed in Table 1. The minimum Renal Failure Risk Score will additionally ensure that participants who are at risk for postoperative kidney events are enrolled [36, 37]. Baseline eGFR (and subsequent measures on days 30, 60, and 90) will be determined using the CKD Epidemiology Collaboration (CKD-EPI) equation based on central measurements of sCysC and/or sCr, as described above.

**Table 1 Tab1:** Description of the key inclusion and exclusion criteria for enrollment in this study

Inclusion criteria	Exclusion criteria
≥ 18– ≤ 90 years of age at the time of informed consent	If expected or planned surgery is: - Emergency or salvage (expected at Screening or Randomization, as assessed by the investigator) - Single-vessel CABG without valve surgery - Surgery conducted without CPB (off-pump)
Body weight ≥ 30 kg at screening period	Any use of KRT or presence of AKI within 30 days prior to randomization (except transient, ≤ 5 days, stage 1 AKI after iodinated contrast exposure); the presence of AKI must be assessed within 72 h prior to randomization
Planned non-emergent cardiac surgery requiring CPB, for these procedures: - Multi-vessel CABG - Valve replacement or repair (ascending aorta surgery permitted if combined with aortic valve replacement/repair) - Combined CABG and valve surgery (inclusion of single-vessel CABG is permitted when combined with valve replacement/repair)	Cardiogenic shock or hemodynamic instability within 72 h prior to randomization (including use of intra-aortic balloon pump or other temporary cardiac output support device, extracorporeal membrane oxygenation, or left ventricular assist device)
Surgery scheduled to occur within 35 days of screening visit (to allow 28 days screening with dosing 1 to 7 days prior to CPB)	Solid organ or bone marrow transplant recipient
Known or apparent CKD (evaluated by history, diagnostic results, or reasonable assessment by the investigator) and eGFR ≥ 20– < 60 mL/min/1.73 m^2^ calculated using the CKD-EPI equation by sCr or sCysC levels, during screening period	History of infection including: - Active systemic bacterial, viral, or fungal infection within 14 days prior to randomization - A history of unexplained, recurrent infection - History of, or unresolved *N. meningitidis* infection

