Approximately 736 participants will be randomly assigned (1:1) using Interactive Response Technology (IRT) and the block randomization method to receive either ravulizumab or placebo, stratified by baseline CKD stage (3a, 3b, 4) and surgery type (mitral valve replacement or combined procedures vs other single procedure). The sample size estimation was based on a two-proportion difference using a normal approximation method to compare the treatment difference in the proportion of participants experiencing MAKE events within 90 days post CPB between the ravulizumab and the placebo group. A sample size of 736 (368 participants per treatment group) has at least 90% power to detect a statistically significant treatment difference of 10% in the proportion of participants with MAKE within 90 days post CPB under a 2-sided significance level of 0.05.

Participants, all investigative site personnel, and any Alexion employee or designee directly associated with the conduct of the study will be blinded to participant treatment assignment throughout the study. The blinding will be maintained by using identical study intervention kits, labels, and appearance of ravulizumab and placebo. The randomization code will be maintained by the IRT provider. In case of an emergency, the investigator has the sole responsibility for determining if unblinding of a participant’s intervention assignment is warranted, primarily based on participant safety. If the investigator decides that unblinding is warranted, the investigator may, at the investigator’s discretion, contact Alexion to discuss the situation prior to unblinding a participant’s intervention assignment unless this could delay emergency treatment for the participant. If a participant’s intervention assignment is unblinded, Alexion must be notified within 24 h after breaking the blind. The date and reason that the blind was broken must be recorded in the source documentation and case report form (CRF), as applicable.

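### The primary CMH analysis is valid, but adjusting also for continuous baseline cystatin C eGFR and the STS renal risk score would add a modest amount of precision for the same estimand

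*Protocol article*

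**What the plan says.** Under Study endpoints, the protocol article defines the estimand as the "population-level treatment difference between the two treatment groups in the proportion of participants experiencing MAKE90" and says that it is "estimated using the Cochran-Mantel Haenszel (CMH) method adjusting for the two stratification variables (surgery type and baseline CKD stage". Under Study assessments and procedures, randomization is "stratified by baseline CKD stage (3a, 3b, 4) and surgery type (mitral valve replacement or combined procedures vs other single procedure". Three stages by two surgery categories gives six cells. No other covariate is named for the primary comparison.

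Two further baseline quantities are planned for everyone before dosing:

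- **Cystatin C eGFR.** Under Study design, "Serum creatinine (sCr) and serum cystatin C (sCysC) will be measured on the day of screening (baseline); day of dosing (day 1", and "Baseline eGFR is reported as the average eGFR calculated from the last assessment during the screening and day 1 visits". The eGFR component of the endpoint is "a decrease from baseline eGFR of ≥ 25% at day 90 calculated using the CKD-EPI equation and sCysC", so this baseline value is its reference.
- **STS renal failure risk score.** Table 1 makes a score of at least 2.8% an inclusion criterion, and Study design says that "the STS score will be calculated during the initial screening period".

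Eligibility eGFR, by contrast, is "calculated using the CKD-EPI equation by sCr or sCysC levels, during screening period". The article does not say which marker defines the CKD stage used for stratification.

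**The concern.** An analysis of a binary endpoint that adjusts for prognostic baseline variables usually estimates the marginal risk difference with a smaller standard error than one that adjusts for fewer. Here the adjustment reduces kidney function to three stages and leaves the STS score out, although the trial itself uses that score to select people at risk of postoperative kidney events. The stage may also be based on creatinine for some participants while the endpoint is based on cystatin C, in which case the strata would follow the endpoint marker less closely.

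What is at stake is efficiency: a somewhat wider confidence interval and slightly lower power than the same participants could give. The validity of the result is not in question.

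**Working it through.** **Inputs.** From the document: 368 per group, 736 in total, a 10-point difference, two-sided alpha of 0.05, at least 90% power, and a normal approximation for two proportions. Not in the document, and so assumed: the event rates, and the share r of outcome variance that the two covariates explain beyond the strata.

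**Step 1. The plan's own figure.** No control rate is given, so 736 can be checked only against assumed rates. At 28% versus 18%:

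- SE = √[(0.28×0.72 + 0.18×0.82)/368] = √(0.3492/368) = 0.0308
- Power = Φ(0.10/0.0308 − 1.96) = Φ(3.246 − 1.96) = 90.1%

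With the pooled-variance formula, power is 89.8% and 90% power needs 742. The stated 736 is therefore consistent with a control rate near 28% and no dropout inflation. Other combinations also come close: 25% versus 15% with 10% dropout gives 746.

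**Step 2. Effect of further adjustment.** Multiply the variance by (1 − r). At 28% versus 18%:

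- r = 0.02: Φ(3.246/√0.98 − 1.96) = Φ(3.279 − 1.96) = 90.6%
- r = 0.07: Φ(3.246/√0.93 − 1.96) = Φ(3.366 − 1.96) = 92.0%

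The half-width of the 95% confidence interval falls from 6.04 points to 5.98 or 5.82. The same precision would need 2×361 = 722 or 2×343 = 686 participants, that is 14 or 50 fewer than 736.

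**Step 3. Other assumed event rates** (same formula):

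| Assumed rates | r = 0 | r = 0.02 | r = 0.07 |
|---|---|---|---|
| 25% vs 15% | 92.8% | 93.2% | 94.3% |
| 28% vs 18% | 90.1% | 90.6% | 92.0% |
| 30% vs 20% | 88.4% | 89.0% | 90.5% |
| 35% vs 25% | 84.6% | 85.3% | 87.0% |

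**Step 4. The starting value.** The r = 0 column is the unadjusted formula, not the power of CMH, which already gains from the strata. Suppose the strata explain 4.9% of outcome variance, as in the middle scenario of step 5. At 28% versus 18% the start becomes Φ(3.246/√0.951 − 1.96) = 91.4%. It rises to 92.0% at r = 0.02 and 93.2% at r = 0.07. The level shifts, but the gain stays at about 0.5 to 2 points.

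**Step 5. Simulation.** 1,500 trials per scenario, N = 736, stratified randomization, an assumed 30% versus 20%. The Mantel-Haenszel risk difference over six strata is compared with standardized logistic regression that adds continuous eGFR and the STS score.

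| Log odds ratio per SD, each covariate | Added share r | Relative efficiency | Power, CMH | Power, standardized |
|---|---|---|---|---|
| 0.2 | about 0.01 | 1.01 | 90.5% | 91.4% |
| 0.4 | about 0.04 | 1.02 | 89.7% | 90.7% |
| 0.6 | about 0.07 | 1.09 | 90.8% | 92.4% |

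A larger run (4,000 trials per scenario) gave relative efficiencies of about 1.01, 1.03 and 1.07 to 1.09, with power changes of about 0, +1.2 and +1.7 points. In the weakest scenario the gain is thus indistinguishable from zero.

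Under the null, the smaller run rejected in 4.8% (CMH) and 5.6% (standardized) of trials, with a Monte Carlo standard error of about 0.6 points. The larger runs gave 4.7% to 5.3% and 4.5% to 5.4%. Mean estimates from the two methods agreed to within 0.0002 in the larger runs, so both target the same quantity.

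**The case against.** The strongest reply is that nothing is wrong. CMH over the stratification factors follows the randomization, estimates the stated difference in proportions and is conventional. The gain is small, and its size depends on prognostic strength that nobody can read from the document. All of that stands.

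Two cautions about the covariates also stand. The STS score predicts STS renal failure, which the article lists as a separate secondary endpoint defined by RIFLE Failure. It does not predict MAKE90 as such, it is truncated at 2.8%, and it may overlap with surgery type and CKD stage. Baseline eGFR may act in two directions: a chance-high baseline makes a 25% fall more likely, while a truly low one plausibly raises the risk of KRT. A single linear term may capture that poorly.

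The cost is also not nil. The method is stated in the protocol article, amendments need ethics and health authority approval, and the second interim analysis covers futility, early efficacy and sample size re-estimation.

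A reader might infer more than the document supports:

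- **That prognostic information is discarded and imbalance goes uncorrected.** Imbalance between stages and surgery types is handled by stratification and again by CMH. What remains is chance imbalance within strata, which the confidence interval already reflects. Baseline eGFR also defines the endpoint and may enter the imputation model, whose variables are not listed.
- **That many participants are stratified on the wrong marker or fall outside the strata.** The article does not say which marker sets the stage, and an article commonly leaves this to the full protocol. Any percentage would be invented, and a mismatch would cost efficiency, not validity.

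**Conclusion.** The point holds as a modest, inexpensive gain in efficiency. It is not an error in the plan. The primary CMH analysis is valid for its estimand but forgoes some precision available from two baseline values planned for every participant.

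If these reduce variance by an assumed 2% to 7% beyond the strata, power at an assumed 28% versus 18% rises by about 0.5 to 2 points over the unadjusted formula value of 90.1%. With weak covariates the gain is near zero. Neither the event rates nor the prognostic strength is in the document, so these figures illustrate a range. The change is worth making because the stated sample size leaves little margin if the control rate is near 28% or higher, and because the simulations showed no shift in the estimand and no type I error beyond Monte Carlo variation.

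**What to change.** Pre-specify as the primary estimate the standardized (g-computation) risk difference from a logistic model with these terms:

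- treatment and the as-randomized strata;
- baseline cystatin C eGFR as a continuous covariate, allowing a non-linear term;
- the log of the STS renal failure risk score.

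Use a robust or delta-method variance, fit the model in each imputed dataset and pool by Rubin's rules. Report the marginal risk difference and not the conditional odds ratio, so that the estimand stays as stated. Keep CMH as the sensitivity analysis and as the pre-specified fallback if the model fails to converge.

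Fix this before the second interim analysis and before any unblinding of the sponsor, and use the same estimator for the efficacy and sample size re-estimation assessments at that look.

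The cost is small: no new data, a wording change that may need a protocol amendment, and alignment of the DMC statistical analysis plan.
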